### Patient and public involvement

Patients and the public were not involved in the development of the trial protocol. However, CDH UK Sparks, as a parent organisation, has assessed and commented on the protocol and has provided start-up funding as also mentioned in the funding statement. This organisation is and will be regularly informed on progress and results of the trial.

### Study procedures

#### ​Baseline assessment

Antenatal ultrasound data about the characteristics of the CDH are collected. These data include the observed/expected lung-head ratio, position of the liver and stomach and the amniotic fluid index. An MRI or an ultrasound is performed depending on local experience and possibilities. If an MRI is performed, the observed/expected fetal lung volume will be calculated. Also data on prenatal interventions are collected. In all mothers, a planned vaginal or caesarean delivery is pursued.

#### ​Randomisation, intervention and blinding

Participants will be randomised using ALEA, which is an online, central randomisation service (https://www.aleaclinical.eu). Allocation concealment will be ensured, as the service will not release the randomisation code until the patient has been recruited into the trial, which takes place after all baseline characteristics have been added. ALEA randomises the patient with a computer-generated randomisation list, made by the independent statistician of the Data Safety and Monitoring Board. Blocked randomisation, with variable block sizes and stratification by centre, is used to achieve equal distribution of the two interventions among the participants.

Postnatally, infants are treated according to a standardised protocol for patients with CDH, which is implemented in all participating centres. This protocol was developed with the available evidence and consensus between the participating centres and was updated in June 2016.^10 16^ If the patient is diagnosed with PH in the first week of life, the patient will be allocated to one of the two study drugs (figure 1). iNO is provided by a tank connected to a ventilator. Different devices are used in different centres. Some centres use integrated systems, making it impossible to disconnect the iNO tank and replace it with another gas to facilitate a blinded intervention. Therefore, the study is open label. iNO is given with a starting dose of 20 ppm, which is the maximum dose.^18 19^ Sildenafil is given intravenously, using a loading dose of 0.4 mg/kg in 3 hours, followed by continuous infusion of 1.6 mg/kg/day.^20 21^ To wean the study drugs a standard protocol is followed (figure 2). The allocated drugs will be restarted as per protocol if criteria for its use are met again before the age of 14 days. To further standardise care, an inotropic support flow chart is included in the study protocol (figure 3). After day 14 treatment of PH will be at the discretion of the local medical team and the study drug can be changed to, for instance, sildenafil orally. The use of bosentan, milrinone and prostin next to the study treatment is allowed. The use of bosentan as add on therapy is allowed and is considered as PH treatment on day 14. The intervention will be prematurely stopped when the patient meets one or more of the defined failure criteria, described in point three of the secondary outcomes. Further treatment will then be at the discretion of the medical team and will be according to the standardised protocol.^16^ iNO and sildenafil can both be given outside the study protocol. An ECMO procedure may then be started in centres where ECMO is available. Data of all patients are used in the intention-to-treat analysis.

**Figure 1 F1:**
[figure not shown]
Trial flow chart. Flow chart showing the steps of the trial, from birth until 12 months. CoDiNOS, Congenital Diaphragmatic hernia Nitric Oxide versus Sildenafil;CDH, congenital diaphragmatic hernia; SAE, serious adverse event; SUSAR, suspected unexpected serious adverse reaction.

**Figure 2 F2:**
[figure not shown]
Protocol to wean study drug. Flow chart showing the protocol to wean off inhaled nitric oxide or intravenous sildenafil. INO, inhaled nitric oxide.

**Figure 3 F3:**
[figure not shown]
Treatment flow chart of systemic hypotension. Flow chart that is added to the treatment protocol, showing the treatment plan for systemic hypotension. LV, left ventricular; SVR, systemic vascular resistance; VA ECMO, veno-arterial extracorporeal membrane oxygenation; ?, if available.

#### ​Follow up

After day 14, additional clinical data, such as time on ventilator support (days) and the use of drugs for the treatment of PH, are collected to answer the secondary outcome questions. Also, echocardiographic measurements are taken at 6 and 12 months to evaluate the presence of chronic PH (table 1).

**Table 1 T1:** Procedures and measurements

	Day 0–7 before start therapy	3 hours after start sildenafil	12 hours after start	8 am after start	24 hours after start	Day of surgery, preoperatively	Day after surgery	Day of ECMO, pre- cannulation	8 am after start ECMO	Day 14	Day 28/before discharge	Day 56	6 months	12 months
Echocardiography	X				X					X	X		X	X
Calculation OI	X		X		X									
Calculation VIS score	X		X		X									
Blood sample	X			X		X	X	X	X	X				
Tracheal aspirate	X			X		X	X	X	X	X				
Urine sample	X			X		X	X	X	X	X				
Severity of CLD											X	X		
Ultrasound brain	X						X							
Sildenafil plasma level		X		X		X	X		X					

CLD, chronic lung disease; ECMO, extracorporeal membrane oxygenation; OI, oxygenation index; VIS, vasoactive-inotropic support.

#### ​Data collection

Echocardiography parameters are measured by local physicians, centrally collected and reviewed by two blinded independent physicians to reduce inter-observer variation. Demographic and neonatal characteristics as well as data on the clinical course of all patients are entered in a password protected web-based database in Rotterdam (OpenClinica). On request the collected data will be available. All centres will keep a logbook of the number of non-participants, including the reasons for not participating. Study documents are securely stored at each study site for 15 years.

#### ​Laboratory testing

Blood, urine and tracheal samples are collected in most centres during the trial. Blood samples are collected before the start of the study and at different time points until day 14. Some samples will be used to externally validate a NONlinear Mixed Effects Modeling (NONMEM) prediction model for sildenafil. The other samples will be used in future research on biomarkers to predict severity and outcome of PH in CDH patients. The samples are centrifuged for 6 min at 3000 rpm.^22^ Thereafter, the plasma is removed and stored at –20°C or colder. The total amount of blood taken is maximal 2.5% of the circulating volume. Blood sampling will only be done if a central or peripheral line is still present and/or in combination with routine laboratory measurements. This way blood sampling is a minimal burden for the patient.

Tracheal aspirate for proteomic analysis is also collected at different time points during routine tracheal suctioning in ventilated patients. Protein profiling with proteomics is used to identify specific groups of proteins that are involved in the pathogenesis of PH. The tracheal aspirates is centrifuged for 6 min at 3000 rpm and stored at –80°C.^23^

Also, 8 hour urine is collected at different time points. Two samples of 5 mL are taken and stored at –20°C or colder.

#### ​Withdrawal of participants

Parents may decide to withdraw from the study at any time without any consequences. The investigator can decide to withdraw a patient from the study for urgent medical reasons. In some cases, there may be exclusion criteria, which were not known before randomisation. If this is the case, the patient will be withdrawn from the study after contacting the study coordinator. With consent of the parents data will still be collected, stored and analysed to perform an intention-to-treat analysis. These children will be treated according to standard practice.^10 16^

### Sample size calculation

The sample size calculation is based on a power analysis for the primary outcome, using previously published data on PH. Lusk *et al* showed that PH, defined as >2/3 systemic blood pressure measured on echocardiography, in CDH patients on day 14 has a positive predictive value of 0.8 for death, death or ventilation, and death or ventilator support. PH on day 14 is observed in 64% of CDH patients.^24^

Even though the definition of the primary outcome is not the same, we assume a similar outcome percentage of 64% for failing the primary outcome in our trial, the absence of PH on day 14 without pulmonary vasodilator therapy and/or absence of death within the first 28 days of life, in the iNO group. Our aim is to promote practice change; therefore, we aim for a clinically significant difference. For a 25% relative reduction to 48%, a sample size of 300 patients (150 patients per group) is needed to obtain a power of 80%. This will match a number needed to treat of 6.25. Taking missing data and the effects of correction for covariates into account, we adjust this sample size to 330 patients. In the collaborating centres 550 patients will be born in 3 years. Based on our earlier trial (CMV Versus HFO in Congenital Diaphragmatic Hernia; VICI trial) we expect to have an inclusion rate of 60%. Therefore, the inclusion of 330 patients should be reached in 3 years.

### Data analysis

The patients will be analysed according to the group they are randomised to (intention-to-treat analysis). A p-value (two-sided) <0.05 is considered significant in all analyses. The primary endpoint will be analysed using multiple logistic regression with randomisation arm, centre, observed/expected head-lung ratio, position of the liver, side of the defect, defect size and ventilation modality as independent variables.^25^ If necessary, multiple imputation using the fully conditional specification method will be used to account for missing data in the independent variables. We will perform a sensitivity analyses with adjustment for the use of prostin and milrinone, to account for the effects of these vasodilators on PH.

The following analyses will be performed for the secondary outcomes. The distribution of VIS score in all study participants will be compared between t=0 and t=12 hours after initiation of drug administration using a Wilcoxon signed rank test. The distribution of changes in OI and VIS score from t=0 to t=12 and t=24 hours will be compared between the randomisation groups with a Mann-Whitney test. The overall mortality in the first year of life will be compared between the randomisation groups with Kaplan-Meier curves and the log-rank test. The number of treatment failures, the need for ECMO (in ECMO centres) and the need for medication for PH or chronic lung disease at discharge, and during the first year of life, will be compared between randomisation groups with χ^2^ tests. The number of study drug free days at day 14, the number of ventilation-free days until day 28, the fraction of days with need for medical treatment (excluding the study drug) for PH during the hospital admission and the severity of chronic lung disease using the Bancalari definition will be compared between randomisation groups using Mann-Whitney tests. Deaths will be counted as the worst outcome in these analyses, in accordance with the intention-to-treat principle. The presence of PH at 28 days/discharge, 6 and 12 months according to the echocardiographic parameters will be compared between randomisation groups with a χ^2^ test.

To externally validate the pharmacokinetic model of sildenafil and its active metabolite (in NONMEM) normalised prediction distribution errors and visual predictive check will be used. Furthermore, the model will be used to predict the drug concentrations from the new data set using simulations, in which we expect that the difference will be less than 20%. To assess whether there is a relationship between the concentration of sildenafil, its active metabolite and the clinical effects, such as OI, VIS score and echocardiography measures, a Mann-Whitney or Student’s t-test will be used.

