### Patients

Infants diagnosed with CDH who have PH in the first week after birth are eligible for the trial if born at or after a gestational age of 34 weeks. The diagnosis of PH is defined as at least two of the following four criteria: (1) systolic pulmonary arterial pressure >2/3 systolic systemic pressure estimated by echocardiography, (2) RV dilatation/septal displacement, RV dysfunction +/−left ventricular dysfunction, (3) pre-post ductal SpO_2_ difference >10%, (4) OI >20. Exclusion criteria are a severe chromosomal anomaly which may imply a decision to stop or not to start life-saving medical treatment, severe cardiac anomaly expected to need corrective surgery in the first 60 days of life, renal anomalies associated with oligohydramnios, severe orthopaedic and skeletal deformities, which are likely to influence thoracic, and/or lung development and severe anomalies of the central nervous system. Patients who are born in another centre and transported with iNO are also excluded from the trial. Patients who received fetal interventions (trachea balloon placement) are not excluded.

Following antenatal diagnosis, the parents are counselled and informed about the study by the clinician or research coordinator. Also, they receive a patient information letter and an informed consent form. If the patient is not born in a participating centre or the diagnosis of CDH was not known, parents are counselled after the diagnosis of CDH and are informed about the study. Also, they receive written information and an informed consent form. This informed consent form contains consent for the trial and for collection of data and material for future research.

For the development of the protocol the SPIRIT reporting guidelines have been used.^17^ This publication is based on protocol V.4, 13 June 2018.

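### Infants not diagnosed before birth have no measured O/E lung-head ratio, and the primary model imputes it without any term marking that absence

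*Protocol article*

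**What the plan says.** Four statements in the Protocol article bear on this.

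- **Source of the ratio** (Baseline assessment): "Antenatal ultrasound data about the characteristics of the CDH are collected", followed by "These data include the observed/expected lung-head ratio, position of the liver and stomach and the amniotic fluid index". Liver position is in the same list.
- **Who can be enrolled** (Patients): "If the patient is not born in a participating centre or the diagnosis of CDH was not known, parents are counselled after the diagnosis". Enrolment is therefore open to infants with no antenatal diagnosis.
- **Primary model** (Data analysis): besides randomisation arm and centre, the model takes "observed/expected head-lung ratio, position of the liver, side of the defect, defect size and ventilation modality as independent variables". No listed term records whether the hernia was known before birth.
- **Missing covariates** (Data analysis): "If necessary, multiple imputation using the fully conditional specification method will be used to account for missing data in the independent variables". No distinction is made between a value that went unrecorded and one that was never measured. The variables in the imputation model are not listed.

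**The concern.** For an infant whose hernia came to light only after birth, O/E LHR is not a sporadic gap. It is missing because of when the diagnosis was made, and that is known before randomisation. Imputation fills the value from infants who were scanned, given the other variables in the imputation model. This assumes that, given those variables, being undiagnosed before birth carries no further information about the ratio. Because the analysis model has no term for it either, it also assumes no further information about outcome. The trial cannot test the first assumption, since no unscanned infant has a ratio to compare.

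What is at stake is precision. If timing of diagnosis does predict outcome, the primary analysis leaves a known baseline fact unused. The increase from 300 to 330 patients already has to cover both missing data and covariate correction, so an avoidable loss is worth preventing.

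**Working it through.** **1. The plan's own figure.** Inputs from Sample size calculation: 64% v 48%, power 80%; two-sided 0.05 from Data analysis. With pooled variance and no continuity correction,

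n per arm = [1.960 × √(2 × 0.56 × 0.44) + 0.842 × √(0.64 × 0.36 + 0.48 × 0.52)]² / 0.16² ≈ (1.376 + 0.583)² / 0.0256 ≈ 150.

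This gives 300 in total, as stated, and 300 × 1.10 = 330. Nothing below changes the planned number.

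**2. Validity.** Simulated trials of 330 infants, 1:1, with a logistic model on arm, the ratio and one correlated covariate. Log odds = 0.6 − 0.8 × ratio − 0.3 × covariate + treatment effect (0 or −0.85). The ratio was unobserved in 10, 20 or 30%, and the true ratio of these infants was shifted by 0 or +1 SD. There were 10 imputations and 1,000 trials per setting. All parameters are assumptions.

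- Type I error with imputation: 4.0 to 5.6%, with a Monte Carlo standard error of √(0.05 × 0.95 / 1,000) ≈ 0.7 points.
- Largest move in the mean treatment log odds ratio against fully observed data: −0.864 to −0.852, a difference of 0.012.
- Power against fully observed data: 0.2 to 2.0 points lower.

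Here late diagnosis acts only through the ratio. The concern is that it may also have its own effect on outcome, so that was added next.

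**3. Power when late diagnosis is itself prognostic.** The links are assumed. Modest means log odds −0.5 for late diagnosis and a ratio +0.5 SD higher; strong means −1.0 and +1 SD. Results for 330 infants and 1,500 trials per setting:

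| Link | Share not measured | Imputation alone | Imputation + indicator | Mean fill + indicator | Gain (points) |
|---|---|---|---|---|---|
| None | – | 83.5% | 83.9% | 84.2% | 0.4 / 0.7 |
| Modest | 20% | 83.1% | 84.1% | 84.1% | 1.0 / 1.0 |
| Modest | 35% | 82.1% | 83.1% | 84.5% | 1.0 / 2.4 |
| Strong | 20% | 78.7% | 83.1% | 83.0% | 4.4 / 4.3 |
| Strong | 35% | 76.8% | 81.0% | 81.7% | 4.2 / 4.9 |

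Type I error was 3.9 to 5.0%. The Monte Carlo standard error of one power figure is √(0.8 × 0.2 / 1,500) ≈ 1.0 point.

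**4. Sensitivity to the other assumed parameters.** Two further simulations used other assumed parameters, so compare gains and not power levels.

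- 3,000 trials per setting, mean fill with indicator v imputation alone. Modest link: 87.1 v 86.8% (10% not measured), 87.1 v 86.4% (20%) and 86.9 v 85.6% (35%), gains of 0.3, 0.7 and 1.3. Strong link: 87.1 v 85.4%, 86.2 v 83.6% and 85.4 v 81.3%, gains of 1.7, 2.6 and 4.1. The paired standard error is 0.3 to 0.5 points, so the 10% modest case is within noise.
- 1,500 trials per setting, strong link, imputation alone / imputation + indicator / mean fill + indicator: 78.5 / 80.5 / 81.1% (20%) and 74.5 / 79.3 / 79.9% (35%).

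**5. Where the gain comes from.** In the last set, keeping imputation and adding the indicator recovers 80.5 − 78.5 = 2.0 of the 2.6 points at 20%, and 79.3 − 74.5 = 4.8 of the 5.4 points at 35%. In the table it recovers all or most of the gain under the strong link. The indicator does the work; dropping imputation does not.

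**The case against.** The strongest reply is that nothing here is wrong. Randomisation makes the missingness independent of arm, and both methods hold the type I error and give nearly the same treatment effect. Choosing covariates is then partly preference. Imputation by fully conditional specification also works conditionally, so an unscanned infant is not simply given a typical scanned infant's value. The list of imputation variables is ordinary SAP material. All of this stands, and it rules out any claim that the planned analysis is biased or that multiple imputation is the wrong tool. It does not remove the point, because the article itself fixes the covariates of the primary model and the method for their gaps.

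The size also rests on assumptions. Every enrolled infant must meet at least two pulmonary hypertension criteria, and outborn infants transported on iNO are excluded. Both may reduce the share or the contrast.

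A reader might infer more than the document supports:

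- **That the ratio cannot exist for these infants.** It was a real fetal quantity that nobody measured, so imputing it is an assumption and not nonsense.
- **That hernias missed before birth are milder.** The article does not say so. The indicator works in either direction.
- **That whole centres lack the ratio.** "An MRI or an ultrasound is performed depending on local experience and possibilities" leaves this possible, but no MRI-only centre is described, and the preceding sentences have the ratio collected from ultrasound.
- **That fetal intervention needs its own term.** "Patients who received fetal interventions (trachea balloon placement) are not excluded" shows that such infants enter, but leaving out one possible covariate is not an error, and no size was worked out. It remains optional.
- **That the loss is 6 points.** A 500-trial run at 35% with a strong link gave 76.6 v 82.6%, but the larger runs put it nearer 4 to 5.

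**Conclusion.** The point holds as a matter of efficiency, not validity. For infants not diagnosed before birth O/E LHR was never measured, and the primary analysis treats that fact as uninformative given the other variables. The treatment comparison and type I error are not at risk.

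Under assumed shares of 10 to 35%, the loss is about 0 to 1 power points with no or a modest link (up to about 2 against mean fill). With a strong link it reaches about 4 to 5 points, and about 2 to 3 at the smaller shares under some of the assumed parameters. The article gives neither the share nor the strength of the link, so the true loss may be negligible. Adding the indicator cost no power even with no link, so it is a free improvement and not a correction of an error.

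**What to change.** Add a baseline indicator for no antenatal O/E LHR measurement to the primary logistic model, and fix one of two routes before the analysis:

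- **Keep multiple imputation** and carry the indicator in the imputation model as well. In the equation for the ratio itself it cannot be estimated, because every infant with an observed ratio has the value 0. It acts in the equations for other incomplete covariates and in the analysis model.
- **Set the ratio to the mean** for these infants, and keep imputation for sporadic gaps in scanned infants.

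The routes should not be chosen after seeing results, since they adjust for slightly different things. In the first simulation, with 30% not measured and no shift, the mean log odds ratio was −0.861 with imputation alone and −0.831 with the ratio set to a constant plus indicator, against −0.862 with full data.

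Liver position is listed among the same antenatal data. State whether a postnatal value may be used. If not, treat it the same way; one indicator serves both where they are missing in the same infants.

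Cost: one extra baseline term, known before randomisation, with no new data and no change to the sample size.

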iNO diffuses rapidly across the alveolar-capillary membrane into the smooth muscle of pulmonary vessels to activate soluble guanylate cyclase. This enzyme mediates many of the biological effects of iNO, and is responsible for the conversion of guanosine triphosphate (GTP) to cyclic guanosine monophosphate (cGMP). The increase of intracellular cGMP relaxes smooth muscles via several mechanisms. iNO also causes bronchodilation and has anti-inflammatory and anti-proliferative effects.^7^ In term and near term infants with persistent pulmonary hypertension of the newborn (PPHN), iNO decreases the median duration of mechanical ventilation and reduces the need for extracorporeal membrane oxygenation (ECMO). However, in the two available randomised controlled trials (RCT) with a small number of patients with CDH, mortality did not improve and more ECMO treatment was needed despite short-term improvement of oxygenation in some treated patients.^8 9^ In the centres of the CDH EURO Consortium, iNO is standard of care in infants with CDH and PH although the positive pharmacodynamic effects in these infants are less convincing than in infants with PPHN.^6 10^ The pathophysiological mechanism of this difference is not understood. In resource poor settings iNO is often unavailable. In the search to find another treatment option, trials to evaluate the effect of sildenafil in newborns with PPHN have been conducted.^11^

Sildenafil is a selective phosphodiesterase type 5 (PDE5) inhibitor. PDE5 is an enzyme that specifically degrades cGMP. Sildenafil inhibits PDE5, increasing cGMP and nitric oxide-mediated vasodilatation of the smooth muscles in arteries. Only five RCTs have been performed in newborns, all non-CDH patients with PPHN. Four of these studies showed a decrease in oxygenation index (OI) and mortality in a setting where iNO was not available, while one trial showed no additional benefit of sildenafil when added to iNO.^11^ Although sildenafil is increasingly used in CDH patients, only retrospective data are available.^12^ A decrease in pulmonary vascular resistance index and an increase in cardiac output were found in a small group of oral sildenafil-treated infants with CDH refractory to iNO.^13^ Intravenous sildenafil improved OI and reversed the right-to-left shunt ratio over the PDA, but it also increased the need for inotropic support.^14 15^ However, its effect on outcome is unknown.

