### Objectives

The primary objective of the study is to determine whether the incidence of PH is lower in CDH patients treated with intravenous sildenafil than in patients treated with iNO, with the primary outcome defined as the absence of PH on echocardiography on day 14 without pulmonary vasodilator therapy and without treatment failure and/or death within the first 28 days after birth. PH is defined as systolic pulmonary arterial pressure >2/3 systolic systemic pressure and/or right ventricular (RV) dilatation/septal displacement and RV dysfunction +/−left ventricular dysfunction.

The secondary outcomes are:

Change in OI after 12 and 24 hours of therapy.Overall mortality.The incidence of treatment failure which is defined as:inability to maintain preductal saturations above 85% (±7 kPa or 52 mm Hg) or postductal saturations above 70% (±5.3 kPa or 40 mm Hg).and/or increase in CO_2_ >70 mm Hg (9.3 kPa) despite optimisation of ventilator management.and/or inadequate oxygen delivery with metabolic acidosis defined as lactate ≥5 mmol/L and pH <7.15 and/or hypotension resistant to fluid therapy and adequate inotropic support resulting in a urine output <0.5 mL/kg/hour.and/or lactate ≥5 mmol/L and pH <7.15.and/or OI consistently ≥40.Time on intervention drug, defined as intervention drug free days after initiation of the intervention, calculated on day 14.Need for ECMO.Ventilator free days on day 28.The use of drugs for PH treatment during the hospital admission.The use of pulmonary and/or cardiac medication at discharge and its total duration of administration.Short-term and long-term PH on echocardiography at 24 hours, 28 days/discharge and 6 and 12 months.The incidence of chronic lung disease.The development of neurological abnormalities evaluated with ultrasound of the brain before the start of the trial, after surgery and before discharge.The external validation of the sildenafil pharmacokinetic - pharmacodynamic (PKPD) model for the pharmacokinetics and the pharmacodynamic effects of sildenafil.

Safety outcomes include adverse events due to the study drugs and the vasoactive-inotropic support (VIS) score.

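### One of the two planned VIS analyses is an uncontrolled before-after test with both arms pooled. It cannot inform the sildenafil-versus-iNO question and should be dropped or made descriptive by arm.

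*Protocol article*

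**What the plan says.** The Objectives section makes VIS a safety outcome: "Safety outcomes include adverse events due to the study drugs and the vasoactive-inotropic support (VIS) score". The Introduction gives a reason to watch it, reporting of intravenous sildenafil in CDH that "it also increased the need for inotropic support".

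The Data analysis section then plans two analyses of VIS.

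- **Pooled, before versus after (Wilcoxon signed rank):** "The distribution of VIS score in all study participants will be compared between t=0 and t=12 hours after initiation of drug administration".
- **Between arms (Mann-Whitney), in the next sentence:** "The distribution of changes in OI and VIS score from t=0 to t=12 and t=24 hours will be compared between the randomisation groups".

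The same section sets one threshold for everything: "A p-value (two-sided) <0.05 is considered significant in all analyses". Table 1 schedules the VIS calculation before the start of therapy and at 12 and 24 hours, which supplies the data for both analyses. The article gives no purpose for the pooled test and does not say which of the two carries the safety conclusion on VIS.

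**The concern.** The first test speaks of all participants and the second of the randomisation groups, so the first one merges the arms. Both arms receive an active drug and there is no untreated group. A before-after change in the merged cohort therefore has nothing to be compared with. It combines any effect of sildenafil, any effect of iNO, the course of the disease and concurrent care over the first 12 hours, and regression to the mean in infants enrolled when their pulmonary hypertension met the entry criteria.

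The trial asks whether sildenafil is better than iNO. The pooled p-value does not bear on that question for benefit or for harm. Because the significance rule covers all analyses, a result below 0.05 could be reported as a significant rise or fall in a safety outcome, and a null result as no change after treatment. Neither statement would rest on the randomisation. The two VIS tests can also disagree, and the article does not say in advance which one counts.

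**Working it through.** **Inputs.** The article gives no SD and no expected change for VIS, so there is no VIS figure to reproduce. The arm size comes from the Sample size calculation section: failure 64% versus 48%, two-sided alpha 0.05, power 80%, 150 per group, raised to 330 in total (165 per group).

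**Reproducing the arm size.** With pooled variance under the null and mean proportion (0.64 + 0.48)/2 = 0.56:

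n = [1.96·√(2·0.56·0.44) + 0.8416·√(0.64·0.36 + 0.48·0.52)]² / 0.16²

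= [1.96·0.7020 + 0.8416·0.6928]² / 0.0256 = (1.376 + 0.583)² / 0.0256 ≈ 150 per group.

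This matches the plan, so 150 per arm is a fair size for the illustration.

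**What each test measures.** Let dS and dI be the mean VIS change under sildenafil and iNO.

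- The pooled test responds to the average, (dS + dI)/2.
- The between-arm test responds to the difference, dS − dI.

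For normal changes with SD 1 and 150 per arm, the approximate standardised signals are

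- pooled: √300·(dS + dI)/2
- between arms: (dS − dI)/√(2/150)

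to be set against the critical value 1.96.

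- Same rise of 0.3 in both arms: pooled √300·0.3 = 5.20; between arms 0.
- +0.25 under sildenafil, −0.25 under iNO: pooled 0; between arms 0.5/0.1155 = 4.33.
- +0.3 under sildenafil, 0 under iNO: pooled √300·0.15 = 2.60; between arms 0.3/0.1155 = 2.60.

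**Simulation of the two planned tests** (2,000 runs per scenario, normal changes, assumed SD 1, 150 per arm; percentage of runs with p<0.05):

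| Mean change, sildenafil / iNO (SD) | Pooled signed rank | Between-arm Mann-Whitney |
|---|---|---|
| 0 / 0 | 5.7% | 5.0% |
| +0.3 / +0.3 | 99.8% | 5.2% |
| +0.25 / −0.25 | 4.8% | 98.7% |
| +0.3 / 0 | 70.8% | 71.7% |

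With 165 per arm the pattern is the same. The last three rows become 100% and 5.2%, 3.7% and 99.6%, and 77.1% and 75.0%.

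**Reading.** In the second row the pooled test is almost always significant with no difference between the drugs. In the third it stays near its nominal level although the arms differ by 0.5 SD. In the fourth, where only sildenafil raises VIS, the two tests reject about equally often, but a pooled rejection still could not be told apart from a trend common to both arms. In each of these rows the between-arm test responds only to the difference between arms.

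**The case against.** A reader who stops at the pooled sentence might infer that it is the VIS safety analysis, and that the plan can therefore hide the inotropic harm it links to sildenafil. The document does not support that. The very next sentence plans the randomised comparison of VIS change at 12 and 24 hours, and Table 1 schedules the measurements for it. Other routes exist as well: the plan relates sildenafil concentration to VIS, and serious adverse events are reported to 12 months.

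Three further arguments can be made for the plan.

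- **The article never says that the signed rank result shows a drug effect.** This is true, but the test has no other stated purpose and is not labelled descriptive, and the significance rule covers it.
- **Exact cancellation needs VIS to fall under iNO as much as it rises under sildenafil, and nothing in the article says that iNO lowers VIS.** This stands. With a rise under sildenafil alone, pooling loses almost no power (70.8% against 71.7%). Cancellation is the weaker half of the concern. The stronger half, that a shared time trend alone produces significance, needs no such assumption.
- **A Mann-Whitney test on change scores is a valid randomised comparison, and estimates with intervals may sit in an analysis plan that is not shown.** This also stands. The adjustment proposed below improves precision; it does not repair an error.

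**Conclusion.** The point holds as a minor one. The pooled signed rank test on VIS is uncontrolled, merges two active arms, and would be called significant at p<0.05 although it cannot attribute a change to either drug or compare them. The harm noted in the Introduction is examined by the planned between-arm test and is not hidden. No primary result, sample size or randomised comparison is affected.

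The percentages rest on assumed normal changes with SD 1 and assumed shifts, because the article gives none. VIS is likely to be skewed, so the true figures would differ. The qualitative result depends only on the fact that one test responds to the average change and the other to the difference.

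**What to change.** 1. Delete the pooled signed rank test, or replace it with a descriptive display of VIS change by arm at 12 and 24 hours, without a p-value.
2. Name the existing between-arm comparison at 12 and 24 hours as the VIS safety analysis.
3. Carry it out adjusted for baseline VIS, which is already collected, and stratified by or adjusted for centre, which is the randomisation stratum. A rank-based or ordinal model suits a score that is likely skewed. Report an estimate of the arm difference with a 95% CI.

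**Cost.** One sentence is deleted or reworded and one or two are added. No new data, patients or procedures are needed. The analysis takes slightly more work than an unadjusted Mann-Whitney test, and one uninformative p-value is lost.
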